### Sample Size

The pilot study was not designed for adequate statistical power but to test the feasibility and potential efficacy of the program [44]. To reach these aims, we estimate that a total of 50 participants should be randomized into each group (experimental and control). This sample size is realistic considering the number of trauma patients admitted in the center where the study will be conducted.

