**Methods:**

A 2-arm pilot randomized controlled trial (RCT) will be conducted in patients presenting a high risk for chronic opioid consumption. Fifty participants at high risk for chronic consumption of opioid will receive either TOPP-Trauma or an educational pamphlet. The feasibility assessment of TOPP-Trauma will be based on the ability to provide its components as initially planned. Several parameters will be evaluated to determine the feasibility of the research methods, including the adequacy of the sampling pool, the dropout rate, and the ease of data collection. The morphine equivalent dose (MED) per day between both groups will be measured at 6 and 12 weeks. Pain intensity and pain interference with activities will also be evaluated at the same time points.

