### Design

The design selected is a two-arm pilot randomized controlled trial, to mirror the elements that would be present in a future full-scale RCT [33]. Particularly, in terms of randomization acceptance to either the experimental or control group for patients with traumatic injuries with a high risk profile for chronic consumption, and the attrition rate in both groups at the end of the study. Two groups will be studied concurrently and followed at the different study time points (T1 to T8) presented in Fig. 1. In addition to standard pain management treatments, the control group will receive an educational pamphlet, while the experimental group will receive the same pamphlet accompanied by a structured follow-up with the TOPP-Trauma research team.

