### Setting

The study will be conducted in a level-1 trauma center in Montreal, Canada, admitting 1400 trauma patients, on average, annually. Ethics committee approval was obtained from the Centre Intégré Universitaire de Santé et de Services Sociaux du Nord-de-l’Île-de-Montréal Research Ethics Board (REB) (project identification number: 2019–1621).

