#### Feasibility and acceptability

A Program Feasibility Evaluation Logbook will make it possible to collect program feasibility data (Table 3) [58]. The Program Feasibility Evaluation Logbook will detail information on the program components that need to be delivered in each session, the pain self-management strategies applied by participants between sessions, the appropriateness of the physical environment in which the program is delivered, the time dedicated to adequately deliver the program and answer patient questions, and the challenges faced when providing the program.

**Table 3 Tab3:** Variables to assess the feasibility of the intervention and the research methods

Variables	Indicators
*Intervention feasibility*	
1- The possibility to deliver the intervention as planned 2- Participants adhering to the intervention	- Provision of ≥80% of planned components of each in-presence session and of the overall intervention [59].
	- Session duration (sessions 1 to 6: 15 min).
	- Challenges faced during session delivery.
	- Attendance to ≥80% of sessions by participants [59].
	- Involvement in intervention activities and implementation of recommended self-management ≥80% behaviors by participants [59].
*Research methods feasibility*	
1- Adequacy of the sampling pool and recruitment time 2- Ease of screening 3- The possibility of applying randomization procedures as planned 4- Attrition rate in experimental and control groups 5- Ease of data collection procedures	- Obtaining consent from ≥80% of patients approached to participate in the study.
	- Percentage of eligible patients who were included in the study. - Patient’s reasons for refusal to participate in the study.
	- Difficulties in obtaining patients’ consent.
	- Recruiting study sample (i.e., 50 participants) in ≤9 months [31].
	- The time required to screen participants relative to recruitment.
	- The time required to obtain consent and baseline data relative to recruitment.
	- Eligibility criteria not limiting the pool of participants by ≥50% [32].
	- Reasons for ineligibility.
	- Difficulties when applying the randomization procedures.
	- Patient acceptance to randomization, either to the treatment or control group ≥80% of the time [32].
	- Attrition rate in experimental and control groups, i.e., ≤ 20% [60].
	- Percentage of questionnaires completed in full.
	- Pattern and rates of non-answered questions at each time measure.
	- Mean time required to complete the outcome questionnaires.

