### Allocation

#### Randomization

The randomization sequence will be generated by a coordinating center, located within the hospital’s research center where the study will be conducted, to keep researchers blinded to allocation. A computerized random-number generator will produce the sequence (i.e., Research Randomizer). Tickets will be placed in sealed, opaque, sequentially numbered envelopes to randomize study participants to either the control or experimental group. Participants will be randomized after collecting baseline data.

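### The Sample Size section calls for 50 participants per group (100 in all), while the Abstract and the Table 3 recruitment indicator give 50 for the whole trial

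*Protocol article*

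**What the plan says.** The article states the sample size in three places.

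- **Sample Size:** "we estimate that a total of 50 participants should be randomized into each group (experimental and control"). The same section explains that "The pilot study was not designed for adequate statistical power but to test the feasibility and potential efficacy of the program", and justifies the number only as realistic given the centre's admissions.
- **Abstract, Methods:** "Fifty participants at high risk for chronic consumption of opioid will receive either TOPP-Trauma or an educational pamphlet". This is one number across both arms.
- **Table 3 (Feasibility and acceptability), research methods indicators:** "Recruiting study sample (i.e., 50 participants) in ≤9 months". This equates the study sample with 50 and attaches the time limit to it.

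Two further statements bear on the arithmetic. The Design section says "The design selected is a two-arm pilot randomized controlled trial", which fixes the number of arms at two. The Randomization section describes envelopes used "to randomize study participants to either the control or experimental group" but gives no allocation ratio.

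**The concern.** The number to randomize cannot be both 50 and 100. The Sample Size section is where a reader looks for the definitive figure, and it disagrees with the other two places.

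Feasibility of the research methods is one of the trial's stated objectives, and recruiting the sample within 9 months is one of its indicators. That indicator is tied to 50. If 100 is the real target, the criterion can be met at half enrolment. If 50 is the real target, the Sample Size section promises twice as many participants as will be recruited. Two readers with the same recruitment data could disagree on whether the target was reached. The total also determines how many randomization envelopes are prepared and how closely the arm-level percentages and the between-group differences are estimated.

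**Working it through.** **Inputs from the article.** Two arms (Design); 50 in each group (Sample Size); 50 in total (Abstract, Table 3); 9 months (Table 3); a threshold of 80% for several indicators, such as session attendance (Table 3); an attrition limit, "Attrition rate in experimental and control groups, i.e., ≤ 20" per cent (Table 3).

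**Assumption.** Equal allocation, because no ratio is stated. The 50-total reading then gives 25 per arm.

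**Plan's own figure.** No calculation can be reproduced: the article gives no significance level, power, effect size or standard deviation. The check is therefore on consistency.

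**Step 1, total.** Sample Size: 2 × 50 = 100. Abstract and Table 3: 50. Ratio: 100/50 = 2.

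**Step 2, recruitment rate implied by the 9-month criterion (total/9).**
- 50/9 = 5.6 per month
- 100/9 = 11.1 per month
- Ratio: 2

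**Step 3, precision of a percentage in one arm.** The 95% half-width is 1.96 × √(p(1 − p)/n), with p = 0.80.
- n = 25: 1.96 × √(0.16/25) = 0.157, or ±15.7 points
- n = 50: 1.96 × √(0.16/50) = 0.111, or ±11.1 points
- Ratio: √2 = 1.41

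The same half-widths apply at the 20% attrition limit, since p(1 − p) is again 0.16.

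**Step 4, precision of a difference in means, in SD units.** The 95% half-width is 1.96 × √(2/n), with n per arm.
- n = 25: 1.96 × √0.08 = ±0.55 SD
- n = 50: 1.96 × √0.04 = ±0.39 SD
- Ratio: 1.41

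If 20% are lost in each arm (20 or 40 remaining), these become ±0.62 and ±0.44 SD.

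The ratios of 2 and 1.41 do not depend on the chosen percentage or SD, provided the allocation ratio is the same under both readings.

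**The case against.** The strongest reply is that this is a drafting slip. The Sample Size sentence itself speaks of a total, which sits awkwardly with assigning that number to each group, and the other two places agree on 50. This stands as a reason to expect that 50 overall was meant. It does not settle the matter: the sentence as written gives 100, and its only justification, that the number is realistic, does not discriminate. The centre is described as "admitting 1400 trauma patients, on average, annually", about 1,050 in 9 months (1400 × 0.75), of which 50 is 4.8% and 100 is 9.5%. A reader might infer from these shares which target is attainable. They cannot show that, because the eligibility criteria restrict entry to an unknown fraction of admissions.

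A second reply is that little depends on the number in an unpowered pilot whose outcome analysis consists of means and percentages. This also stands in part. No error rate or power claim is affected, the missing power calculation is not a fault, and recruitment is one of many indicators. The enrolment target and that indicator remain contradictory.

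A reader might also infer that all precision differs by a factor of two. That is true of variance only; interval widths differ by 1.41. Nor does the 80% example extend to every threshold in Table 3: the consent criterion is measured among patients approached, so neither 25 nor 50 is its denominator.

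**Conclusion.** The contradiction is real and visible on the face of the article: 100 in the Sample Size section against 50 in the Abstract and Table 3, with nothing to reconcile them. The enrolment target and the implied monthly recruitment rate differ by exactly two. Interval widths differ by about 1.41. The factor of two in the target needs no assumption; the per-arm figures rest on equal allocation, which the article does not state.

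It should be corrected before the recruitment indicator is judged. The article does not support the further inferences that the team would declare success at half enrolment, or that the pilot is too small for its purpose. It shows only that the criterion as worded would permit the former.

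**What to change.** State one total and one per-group number, state the allocation ratio, and make the Sample Size section, the Abstract and the Table 3 indicator agree.

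- **If 50 in total is meant**, as two of the three places indicate, change only the Sample Size sentence, for example to: fifty participants in all will be randomized across the two groups (25 per group if allocation is 1:1, to be confirmed). Cost: one sentence, and no additional participants.
- **If 100 in total is meant**, leave the per-group number, remove the word that makes 50 a total, and change the Abstract and the Table 3 indicator to 100. Cost: three small edits, plus 50 participants beyond the number now in the Abstract and Table 3. The team would also have to confirm that the 9-month limit still applies at 11.1 per month.

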### Recruitment

Research assistants (RA) will identify potential participants and explain the study. If patients meet the inclusion criteria and wish to participate, after receiving detailed information on what the study entails, the RA will obtain their written informed consent. A RA will then administer the screening tools to determine the presence of risk factors for chronic opioid consumption. Only patients with pre-established risk factors will be included in the study.

### Allocation

#### Randomization

The randomization sequence will be generated by a coordinating center, located within the hospital’s research center where the study will be conducted, to keep researchers blinded to allocation. A computerized random-number generator will produce the sequence (i.e., Research Randomizer). Tickets will be placed in sealed, opaque, sequentially numbered envelopes to randomize study participants to either the control or experimental group. Participants will be randomized after collecting baseline data.

#### Blinding

The expert trauma nurse and the pharmacist who will administer the program will not be blinded to group assignment. To ensure participant blinding to group assignment, the TOPP-Trauma educational session and the educational pamphlet will be given to participants in an office, in private hospital rooms, or in hospital rooms with no other trauma patients present. The RA who will collect and enter the data will be blinded to group assignment. A numerical code will be assigned to each participant, in both groups, to ensure statistician blinding.

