### Intervention

#### Control group

Participants randomized to the control group will receive the standard pain management intervention, consisting in non-opioid analgesics and opioids to control pain, as well as an educational pamphlet. The pamphlet will be provided to participants by the interventionist before hospital discharge, with no specific guided sessions, reflecting what is most commonly implemented in clinical practice. Furthermore, we hope to determine if patients receiving only an educational pamphlet are more likely to drop out than patients with follow-up. We also wish to explore if education at hospital discharge is sufficient to reduce long-term consumption of this type of analgesic.

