#### Program structure

TOPP-Trauma combines two 10-minute educational sessions within the week prior to hospital discharge, and a maximum of six 15-minute opioid tapering counseling sessions every two weeks following discharge (Table 1). A trauma case manager nurse, a nurse practitioner student or the trauma service pharmacist, who have more than five years of experience in caring for the trauma population along the acute continuum of care will provide the counseling sessions. These clinicians will receive a 4-hour training session by the principal investigator on the conceptual underpinnings of the program, the tools used in the study, and on how to deliver the program through role-play. Moreover, meetings will be held every two weeks between the PI and clinicians who will provide TOPP-Trauma until 10 patients will be recruited and until they will have provided the entire program in at least two patients.

**Table 1 Tab1:** TOPP-Trauma Sessions

Sessions	Timing of Delivery	Components
Educational - 1	The week prior to hospital discharge	- The various components of pain (introduction to the biopsychosocial dimensions of pain and how they negatively or positively influence pain experience)
		- How to assess pain intensity
		- Adequate use of analgesics prescribed
		- Need to taper opioids to prevent abuse and dependence
		- How to use cryotherapy
Educational - 2	The week prior to hospital discharge	- How to use deep breathing relaxation exercises
		- The need to stay active
		- How to establish objectives for staying active with the SMART^a^ procedure (establish an objective with the participant)
		- The influence of sleep hygiene on pain and the characteristics of an adequate sleep hygiene
		- The strategies to achieve adequate sleep hygiene
Counseling - 1	One week after hospital discharge	- Assessment of patient’s average pain intensity at rest and upon movement in the last 48 h
		- Follow up on activity objective
		- Assessment of analgesics taken over the last 72 h.
		- Assessment of non-pharmacological pain management strategies used over the last 72 h and underscoring the importance of using these strategies.
		- Providing information on how to gradually reduce the consumption of analgesics (e.g., 25% opioid dose reduction OR decrease frequency of opioid use, e.g., every 6 h instead of every 3–4 h OR before activities causing high-intensity pain) if pain < 4/10 and does not interfere with activities.

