### Variables and Measurement Tools

#### Morphine equivalent dose/day

Opioids taken by participants will be measured by calculating the total morphine equivalent dose (MED) per 24 h, as recommended for studies on the consumption of opioids, using the appropriate conversion methods [61, 62]. Participants will be asked to self-report their opioid use for the last three days and the day associated with the highest MED will be retained. The MED/day will be measured at 6 weeks after the beginning of TOPP-Trauma, since some studies found that a great proportion of trauma patients do not use opioids beyond this period of time [22], as well as at 12 weeks after initiating the intervention. The medical file will be consulted to determine the highest MED over three days before participant randomization, as part of baseline assessment. A pharmacist, blinded to patient allocation, will compute the MED per day.

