### Study limitations

There is a potential social desirability bias to this study since participants will self-report their opioid use at 6 and 12 weeks. The opioid delivery records provided by the community pharmacy, close to both follow-up time points, should help counter this, validating the participants’ assertions. This procedure will also make it possible to document the total quantity of opioids taken by participants, from hospital discharge to 6 weeks after the beginning of TOPP-Trauma, and from 6 weeks to 12 weeks.

The use of an educational pamphlet only for the control group is another limitation to consider. Indeed, experimental group participants could be more inclined to reduce their consumption of opioids because of the attention they will receive from clinicians and not the intervention per se. Despite the fact that preventing the chronic opioid consumption in high risk trauma patients likely require coaching from qualified health professionals, this limitation will be acknowledged in the interpretation of findings on TOPP-Trauma potential effect. Likewise, we will plan to use a three-arm full-scale efficacy trial to account for the attention received while testing TOPP-Trauma impacts.

Finally, participants from both groups will have to answer numerous questionnaires over a 12-week period, which could induce a participation burden. Moreover, the experimental group will have to attend several program sessions. To avoid drop out and loss to follow-up, participants will complete their sessions and questionnaires at the outpatient surgical clinic while waiting to meet their surgeon, whenever possible.

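### The participant-blinding claim cannot hold when one arm gets a pamphlet and the other up to eight sessions, and follow-up outcomes are self-reported

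*Protocol article*

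**What the plan says.** The Blinding section claims masking of participants to their arm and gives one means, a private place of delivery: "To ensure participant blinding to group assignment, the TOPP-Trauma educational session and the educational pamphlet will be given to participants in an office". The same section says the data-collecting research assistant (RA) is blinded, that numerical codes blind the statistician, and that "The expert trauma nurse and the pharmacist who will administer the program will not be blinded to group assignment". The section on morphine equivalent dose adds: "A pharmacist, blinded to patient allocation, will compute the MED per day".

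The arms differ openly. The control pamphlet comes "with no specific guided sessions, reflecting what is most commonly implemented in clinical practice". Under Design, "the experimental group will receive the same pamphlet accompanied by a structured follow-up with the TOPP-Trauma research team". Program structure sets this follow-up at "two 10-minute educational sessions within the week prior to hospital discharge, and a maximum of six 15-minute opioid tapering counseling sessions".

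At 6 and 12 weeks, MED per day is the participant's own report of the last three days (highest day kept), and the BPI is the participant's own rating. Study limitations admits social desirability bias in self-reported opioid use and offers community pharmacy records as a check. It says these records will also "document the total quantity of opioids taken by participants".

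**The concern.** A blinding statement tells the reader which biases the design has removed. This one says that participants' knowledge of their arm has been removed, and it has not. The step described covers only the hand-over of the educational session or pamphlet. Nothing is said to mask the later counseling by phone or in clinic.

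This matters because of how efficacy is measured. One arm is advised at each session to reduce opioid intake when pain allows, and is then asked how much it takes. The other arm is asked the same question without that coaching. If coached participants under-report more, MED per day and the opioid-free percentage move in the program's favor without any true effect. Study limitations treats social desirability as common to all participants. Its separate remark on attention concerns a real change in consumption, not a change in reporting.

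No formal efficacy test is planned. What is at stake is the credibility of the within- and between-group differences that the Discussion offers as an adequate basis for a full trial, and the risk that the blinding claim carries over into that trial.

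**Working it through.** The plan gives no figure for this point, so the check is a comparison of sections, followed by arithmetic on contact and an illustration of size.

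**1. Contact by arm** (Control group; Program structure; Table 2)
- Control: one pamphlet encounter, 0 guided minutes.
- Experimental: 2 + 6 = 8 sessions at most, which agrees with S1 to S8 in Table 2. Maximum time is 2 × 10 + 6 × 15 = 110 minutes.
- Counseling ends early if opioids stop, so 8 sessions and 110 minutes are ceilings. A participant who stops early is still planned to have the two educational sessions.
- Table 2 places S5 at 6 weeks. By the first follow-up, a participant still in counseling has had S1 to S4 (2 × 10 + 2 × 15 = 50 minutes), or S1 to S5 (2 × 10 + 3 × 15 = 65 minutes).

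**2. Can participants know their arm?**
- Recruitment: they consent after a detailed explanation of the study.
- Table 3: acceptance of randomization to either arm, at least 80%, is a feasibility indicator.
- Control group: the investigators want to learn whether pamphlet-only patients drop out more than those with follow-up.

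The last two items sit badly with participants who do not know their allocation. With step 1, they leave no route by which a private room could mask the arm.

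**3. Which outcomes are exposed?**
- MED per day: taken from the medical file at baseline (not exposed), self-reported at 6 and 12 weeks (exposed).
- BPI: patient-rated throughout. The follow-up values are exposed.
- Pharmacy records: not self-reported, but they measure supply. The section on community pharmacy delivery describes what pharmacies prepared and delivered, whereas Study limitations describes quantity taken.

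**4. Illustrative size**

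Let p be the true proportion still using opioids in both arms (no true effect), and m_E and m_C the proportions of users who report none in each arm. The false difference in opioid-free rate is p × (m_E − m_C).
- p = 0.35, the upper figure in the Background for chronic use in trauma patients.
- m_C = 0 and m_E = 0 to 0.20. Both are assumptions; the documents give neither.
- m_E = 0: 0.35 × 0 = 0 points. m_E = 0.10: 0.35 × 0.10 = 3.5 points. m_E = 0.20: 0.35 × 0.20 = 7 points.
- Equal misreporting in the two arms gives 0 whatever its level.

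**5. Comparison with sampling error**

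At 65% opioid-free in both arms, the 95% margin on the difference is 1.96 × √(2 × 0.65 × 0.35 / n).
- n = 25 per arm (50 in total, as in the Abstract, split equally): about ±26 points.
- n = 50 per arm (as in Sample Size): about ±19 points.

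**The case against.** The strongest reply is that little hangs on the sentence. The pilot disclaims power, its efficacy analysis is descriptive, no primary efficacy outcome is named, and the feasibility indicators are largely unaffected. A false difference of up to 7 points lies well inside a margin of 19 to 26 points. Study limitations already discloses social desirability and unequal attention, brings in pharmacy records, and plans a three-arm full trial.

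Most of this is fair and limits the weight of the point. It does not rescue the claim. Noise does not cancel bias, the three-arm plan addresses attention rather than reporting, and none of these passages says that participants will know their arm.

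A reader might also infer more than the documents support:
- **That the RA's blinding fails.** Study limitations says "participants will complete their sessions and questionnaires at the outpatient surgical clinic" while waiting for the surgeon, but only whenever possible. Follow-up may also be by phone, and both arms attend the surgical clinic. Table 2 shows a session alongside an outcome assessment only at 6 weeks, and this applies only to those still in counseling. The realistic route is a participant telling the RA, which is a risk and not a stated failure.
- **That the acceptability questionnaire unblinds the RA.** It falls due at the 12-week closeout, but the Procedure section does not list it among the RA's follow-up tasks.
- **That one pharmacist both delivers sessions and computes MED.** One is described as unblinded and the other as blinded. Read together, the sections imply different people, although neither says so.
- **That a six-week supply is to be checked against a three-day report.** Study limitations describes validation by records near each time point and, separately, a cumulative total. It does not state that comparison.

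**Conclusion.** The participant-blinding claim is wrong as written and should be corrected. This rests on the plan's own description of the arms and needs no outside assumption.

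The consequence is a possible arm-differential bias in follow-up MED per day and BPI, most plausibly in the program's favor. The documents do not determine its size. The range of 0 to 7 points in opioid-free rate rests on 35% continued use, on an assumed 0% to 20% misreporting among experimental-arm users, and on none in controls. It is an illustration, and a reader should not take it as an estimate of bias in this trial.

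The limitation as written is too general because it does not separate the arms, and its wording on pharmacy data equates supply with intake. The RA and pharmacist points are risks to close, not contradictions in the plan.

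**What to change.** 1. In Blinding, replace the participant claim with a statement that participants and program providers are not blinded, and that only the data-collecting RA, the pharmacist who computes MED and the statistician are. The private setting can stay, described as a way to limit contact between participants.
2. State that the pharmacist who computes MED delivers no sessions.
3. Collect MED and BPI before any session held on the same day, and instruct participants not to tell the RA their arm.
4. In Study limitations, name arm-differential self-report as a limitation distinct from general social desirability and from attention.
5. Describe pharmacy data as dispensed throughout, and report cumulative dispensed MED by arm at 6 and 12 weeks beside self-report. The section on potential efficacy does not name this comparison. Dispensed supply is not intake, but it does not depend on what a coached participant chooses to report.

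The cost is a few sentences, an order rule for clinic days and one extra table from data already to be collected. The downside is a less favorable blinding statement.
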